### Secondary outcome measures

For those patients established on dialysis, successful use of the fistula, determined by its use for dialysis on 3 separate occasions during the 10 weeks after the AVF surgical creation.Clinical suitability for dialysis based on examination alone according to local practice, assessed 10 weeks after AVF surgical creation.Formation of a new fistula (including fashioning of proximal neoanastomosis) or radiological salvage procedure, measured by collecting the number and type of these interventions during the 10 weeks after AVF surgical creation.Fistula thrombosis rate: the number of fistulae that thrombose during the 10 weeks after surgical creation.Secondary fistula patency rate: measured by the time interval (in days) between AVF creation until abandonment of the AVF, including all radiological and surgical salvage procedures in between, during the 10 weeks after AVF surgical creation.Patient acceptability based on the proportion of patients that complete their study US scans 10 weeks after AVF surgical creation.

### Blinding

Both the patient and the treating clinical team will be blinded to the results of the Doppler US.

The only acceptable reasons for unblinding are:The participating centre’s local standard of care requires a scan, or a clinical need for a scan is identified, in which case the centre will have access to study scan data for that time point (but not the other study scans) to avoid unnecessary additional scans being scheduled, or:During a trial scan, the AVF is seen to be thrombosed, in which case this information would be shared with the clinical care team to enable appropriate care to continue. In such cases, no further study scans would be required. Clinical outcome data will still be collected at week 10.

### Sample size

We have estimated that 20% of fistulas fail early and that early US has a positive predictive value (PPV; number of true positives/number of predicted positives) of 72% for predicting non-maturation. To estimate this with ±10% precision (ie, the 95% CI is from 62% to 82%), 78 predicted failures are required. We estimate that US predicts failure in 25% of fistulas meaning 312 fistulas are required in the study. Allowing for 10% dropout, 347 fistulas will be recruited. To predict primary fistula patency for the phase II trial (not part of this protocol), we anticipate that two models will be required and therefore we will have two PPVs—one for wrist fistulas and one for elbow fistulas. Assuming a ratio of 50:50 for wrist to elbow fistulas, the precision CI will be from 55.3% to 85.2%.

### Analysis plan

All analyses will be performed according to intention to treat. The analysis population will include all participants enrolled into the study, including those whose fistula failed within the first 2 weeks postsurgery and those enrolled in error.

#### Interim monitoring and analyses

The feasibility of recruitment will be assessed based on data between month 3 and month 9 of the recruitment period. Stop–go criteria for expanding to complete the full first phase trial will be used. The trial will be stopped if fewer than 80 patients have been recruited, additional centres will be recruited if fewer than 120 patients have been recruited, otherwise the trial will continue as planned.

#### Analysis of primary and secondary outcomes

The primary fistula patency rate at week 10 will be calculated alongside an exact 95% CI based on all participants enrolled. It will also be calculated based on participants whose fistulas did not fail early. Patency will be assessed using the results from each US scan up to week 10.

The secondary outcomes will be presented using descriptive summary statistics.

Mixed multivariable logistic regression will be used to model primary fistula patency by 10 weeks, which will then be used as a risk-score calculator in the phase II trial. Two models will be built, one for wrist fistulas and one for elbow fistulas. Measurements taken from the first scan performed at week 2 will be considered as parameters in the model initially, and further parameters from either the second scan or the third scan will then be considered. The choice of second or third scan will be based on the best fitting parameters, as assessed by significance level. A random effect for the participant will be included in the models to account for multiple scan data per participant. The aim will be to build parsimonious models, which contain the minimum number of measurements required to effectively predict primary fistula patency. A receiver operating characteristic curve analysis of the developed risk scores will be used to assist decisions regarding an appropriate cut-off for an indicator for when intervention is required for both wrist and elbow fistulas. The PPV will be calculated alongside an exact 95% CI for the chosen risk score cut-off.

It is anticipated that some participants will not attend all scans, and therefore, some scan data will be missing. Levels of missing data will be summarised for each of the scan time points and will be considered when choosing which scan results to use in the final model. Any missing primary and secondary outcome data will not be imputed. Missing data for parameters in the modelling of primary fistula patency will be imputed using multiple imputation if the level of missing data is greater than 10%.

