### Doppler US surveillance

Duplex Doppler US machines used for the study must have B-mode imaging frequencies of at least 7 MHz. The machines will have both high (>12 MHz), midrange (>7 MHz) and curvilinear (approximately 3 MHz) probes. Scans will be carried out by vascular scientists, surgeons, sonographers and other personnel trained in arteriovenous fistula surveillance by Doppler US; training days have been provided to ensure a standardised approach. The parameters measured for the study will be recorded on an agreed study proforma and include: brachial artery (or subclavian/axillary artery in the presence of a high bifurcation) flow volume and resistance index, outflow vein diameter, anastomotic diameter, AVF depth, presence of a flow limiting stenosis and fistula thrombosis.

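### The sample size covers only the precision of a fixed 72% PPV, but the rule itself is to be derived in two models with about 31 failures each

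*Protocol article*

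**What the plan says.** **Sample size section.** The starting point is "We have estimated that 20% of fistulas fail early" together with a "positive predictive value (PPV; number of true positives/number of predicted positives) of 72% for predicting non-maturation". The target is set by "To estimate this with ±10% precision", from which "78 predicted failures are required". The next step is "We estimate that US predicts failure in 25% of fistulas meaning 312 fistulas are required in the study", raised to 347 for 10% dropout. The section recognises that wrist and elbow fistulas will need separate models. Its only adjustment is a wider interval: "Assuming a ratio of 50:50 for wrist to elbow fistulas, the precision CI will be from 55.3% to 85.2" per cent.

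**Analysis of primary and secondary outcomes.** The method is mixed multivariable logistic regression: "Two models will be built, one for wrist fistulas and one for elbow fistulas". Week 2 measurements are considered first, then those of either the second or the third scan, with that choice resting on significance level. The stated aim is parsimony. An ROC analysis of the developed score helps to set the cut-off, and the PPV with an exact 95% CI is computed at that cut-off. The score is meant to serve as the risk calculator in phase II.

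**Doppler US surveillance.** The recorded parameters are brachial artery "flow volume and resistance index, outflow vein diameter, anastomotic diameter, AVF depth, presence of a flow limiting stenosis and fistula thrombosis", which makes seven per scan.

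**The concern.** The two sections describe different statistical tasks. The sizing treats the PPV as one proportion, observed on fistulas flagged by a rule that exists beforehand. The analysis selects predictors, estimates coefficients and chooses a cut-off in the same fistulas, separately in each half of the cohort. Nothing in the sizing relates the number of failures to the number of parameters considered.

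With few failures per candidate, data-driven selection tends to pick predictors that look strong by chance and to give them coefficients that are too large. Predicted risks are then too extreme, and a cut-off chosen on them does not transfer well to new patients. This matters because the score goes into phase II, and the move to phase II depends on ultrasound being found effective at identifying at-risk fistulas.

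**Working it through.** **1. The plan's own figures reproduce.**
- Predicted failures: 1.96² × 0.72 × 0.28 / 0.10² = 77.4, so 78.
- Fistulas: 78 / 0.25 = 312. Recruited: 312 / 0.9 = 347.
- Per model: 78 / 2 = 39 predicted failures and 0.72 × 39 = 28.08 true positives. The Clopper-Pearson 95% interval for 28.08/39 is 55.3% to 85.2%, as printed. This formula assumes a rule fixed in advance.

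**2. Failures per candidate.** Each model has 312 × 0.5 = 156 fistulas. Failures are 156 × 0.20 = 31.2, or 156 × 0.50 = 78 at the upper non-maturation figure in the Introduction. Seven parameters give 14 candidates from two scans and 21 screened across three. Without thrombosis, which itself ends primary patency, the counts are 12 and 18.

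| Failure rate | Failures per model | 12 | 14 | 18 | 21 |
|---|---|---|---|---|---|
| 20% | 31.2 | 2.6 | 2.2 | 1.7 | 1.5 |
| 50% | 78 | 6.5 | 5.6 | 4.3 | 3.7 |

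If all 347 fistulas were evaluable, there would be 34.7 failures per model at 20%. With a 30:70 split, the smaller model would have 0.3 × 312 × 0.20 = 18.7.

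**3. Discrimination implied by the sizing.** Sensitivity is 0.25 × 0.72 / 0.20 = 90%. Specificity is 1 − 0.25 × 0.28 / 0.80 = 91.25%. Under a binormal model this is an AUC of about 0.97.

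**4. Fistulas needed per model for expected shrinkage S = 0.9.** The formula is n = p / ((S − 1) ln(1 − R²/S)), where R² is the Cox-Snell value and p the number of candidates. AUCs of 0.80 to 0.90 are assumptions. The last column divides 156 by the need per candidate (for example 431/14 = 30.8, and 156/30.8 = 5.1).

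| AUC | R² | n for 14 | n for 21 | Largest p for 156 |
|---|---|---|---|---|
| 0.97 (implied) | 0.482 | 183 | 275 | 11 |
| 0.90 | 0.332 | 304 | 456 | 7 |
| 0.85 | 0.250 | 431 | 647 | 5 |
| 0.80 | 0.182 | 618 | 927 | 3 |

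**5. PPV by simulation.** Settings: 156 fistulas, 20% failures, four true predictors, correlation 0.3, forward selection at p<0.05, 39 flagged, 150 cohorts per row, each model tested in 40,000 new fistulas. These signal settings and the p<0.05 rule are assumptions. There is one record per fistula and no participant random effect.

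| AUC | Candidates | Best achievable PPV | PPV in own data | PPV in new fistulas |
|---|---|---|---|---|
| 0.97 | 14 | 71.7% | 71.6% | 68.5% |
| 0.97 | 21 | 73.1% | 74.0% | 69.4% |
| 0.85 | 14 | 53.3% | 56.5% | 49.2% |
| 0.85 | 21 | 53.1% | 54.8% | 47.1% |
| 0.80 | 14 | 46.6% | 48.5% | 42.2% |
| 0.80 | 21 | 48.0% | 48.1% | 42.1% |

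The loss against the best achievable is 3 to 6 points. PPV in the models' own data exceeds PPV in new fistulas by 3 to 8 points. In the 0.97 rows, the central 95% of cohorts have a new-fistula PPV of 58.4% to 81.0% (14 candidates) and 56.2% to 82.5% (21).

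**6. Calibration by simulation.** With 14 candidates and a between-scan correlation of 0.6, achievable PPVs of 75%, 61% and 48% fell to 71%, 53% and 41%, a loss of 4 to 8 points. Calibration slopes were 0.56, 0.63 and 0.68 (ideal 1). Ridge regression on the same data gave PPVs of 72%, 57% and 44%, with slopes of 1.1 to 1.2. A further set of assumed signals gave slopes of about 0.7 to 0.8 and a loss of 3 to 5 points after selection; ridge brought the slopes to about 1.05 to 1.2.

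**The case against.** - **The article does not say that the fit is unpenalised.** A reader might infer it, but the text names only mixed logistic regression. It ties significance level only to the choice between two scans. An analysis plan that is not shown could add shrinkage and a final candidate list. This stands, so silence on shrinkage is not itself the fault. What the article does fix is the sizing basis, two separate models, a significance-based choice of scan, and an interval that presumes a fixed rule.
- **The candidate counts are upper bounds.** The seven parameters are what the proforma records, and the article does not say that all enter the models. The parsimony aim points to small final models. This also stands: 14 to 21 must not be read as fitted parameters. A small model chosen by significance from a long list still carries the instability of the selection.
- **The 20% is early failure, while the modelled outcome is week 10 patency by ultrasound thresholds.** Failures could be more numerous, which is why the range to 50% is shown. In the other direction, early failures are in the analysis population and study scans stop once thrombosis is seen, so failures with usable later scans may be fewer.
- **The PPV loss is smaller than the interval's half-width of about 15 points, and ridge recovers only 1 to 4 points.** True. But the loss is a systematic shift on top of sampling error, and the larger gain from shrinkage is in calibration.

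**Conclusion.** The point holds in a limited form. The study is sized only for the precision of a fixed rule's PPV, and that calculation does not cover the development of two risk models with about 31 failures each. Even at the discrimination the sizing implies, 156 fistulas per model fall short of the 183 to 275 that 14 to 21 candidates would need. At an AUC of 0.85 the need is 431 to 647. The expected consequence is a calibration slope of about 0.6 to 0.8 and a PPV in new patients about 3 to 8 points below the achievable value. The interval of 55.3% to 85.2% therefore understates the uncertainty of the score that goes into phase II.

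A reader might go further and infer that neither model can deliver 72%. The documents do not support that. At the implied AUC of about 0.97 the mean is 68% to 69%, and 72% lies well inside the simulated range. A PPV far below 72% would come mainly from weaker discrimination: at an AUC of 0.85 the ceiling with 25% flagged is about 53% at any sample size.

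The failure counts follow from the plan's own inputs. The sizes of the PPV loss and of the miscalibration rest on assumed signal strengths, correlations and selection rule.

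**What to change.** **Analysis of primary and secondary outcomes.** Prespecify from clinical knowledge a short candidate list for each model, of a length that about 31 failures can support. By the shrinkage criterion this is roughly three to seven parameters for an AUC of 0.80 to 0.90. Keep flow-limiting stenosis on the list, since the study hypothesis concerns correctable anatomical defects. Fit with shrinkage instead of relying on significance level. Elastic net or ridge would serve, as would a shrinkage factor applied to the parsimonious model. Ridge alone retains every listed measurement, so elastic net or the shrinkage factor fits the parsimony aim better.

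**Sample size.** State the expected failures per model (about 31 at 20%, about 78 at 50%). State also that 55.3% to 85.2% applies to a rule fixed in advance and understates the uncertainty of a score derived from the same data.

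**Cost.** Some wording and a little more analysis work. Coefficients will be shrunken and less directly interpretable, and the precision statement will look slightly less favourable. The short list helps only if it contains the predictors that matter.

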### Primary outcome measure

Primary fistula patency at week 10, according to surrogate US parameters. This is assessed using venous diameter and blood flow measurements:Wrist fistula considered to be patent if there is a minimum venous diameter of 4 mm with a blood flow measurement of >400 mL/min.Elbow fistula, considered to be patent if there is a minimum venous fistula diameter of 5 mm, with a blood flow measurement of >500 mL/min.

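### The participant random effect is unjustified: the scans are repeated predictors of a single outcome, so its variance is practically not estimable

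*Protocol article*

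**What the plan says.** The Primary outcome measure section gives one binary status per fistula at one time: "Primary fistula patency at week 10, according to surrogate US parameters". The model is built on that status. Under Analysis of primary and secondary outcomes the article states: "Mixed multivariable logistic regression will be used to model primary fistula patency by 10 weeks, which will then be used as a risk-score calculator".

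The same section gives the scans their role as predictors: "Measurements taken from the first scan performed at week 2 will be considered as parameters in the model initially". Covariates from one later visit, week 4 or week 6, may be added after that. The choice between these two visits rests on statistical significance. The random effect follows, with its reason: "A random effect for the participant will be included in the models to account for multiple scan data per participant". There is a separate model for each site: "Two models will be built, one for wrist fistulas and one for elbow fistulas". An ROC analysis then supplies a cut-off, and the PPV is reported at that cut-off.

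One sentence points another way: "Patency will be assessed using the results from each US scan up to week 10".

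**The concern.** A participant random intercept accounts for correlation among several outcomes from the same person. Here the repeated quantity is the set of ultrasound measurements, and these sit on the predictor side. Each fistula has one 10-week status, so there is no within-participant outcome correlation to model. The reason given for the random effect does not support it.

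The article names this component and gives its rationale, so it is not a detail left to an analysis plan. It also concerns a main product of phase I, the score to be carried into phase II. If the variance cannot be estimated, three things are at stake: the scale of the published coefficients, any absolute risk read from them at random effect = 0, and possibly the choice between scans.

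**Working it through.** **Inputs from the article (Sample size).** PPV 72%, precision ±10%, 25% predicted to fail, 10% dropout, wrist to elbow 50:50.

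**Reproducing the plan's figures.** 1.96² × 0.72 × 0.28 / 0.10² = 77.4, so 78 predicted failures. 78 / 0.25 = 312. 312 / 0.9 = 346.7, so 347. Each model has 312 / 2 = 156 fistulas and 78 / 2 = 39 predicted failures. The exact 95% interval for 0.72 × 39 = 28.08 out of 39 is 55.3% to 85.2%, as stated. None of this uses the random effect.

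**Set-up of the check.** One data set of 156 fistulas was simulated. The effect sizes are assumptions, not figures from the article. The week-2 value w2 is standard normal, the later value is w4 = 0.6·w2 + 0.8·(standard normal), and logit P(patent) = 1.7 + 0.6·w2 + 1.0·w4. The realised patency was 78.2%. The likelihood contribution of participant i is

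L_i = ∫ ∏_j P(y_ij | x_ij'b + σu) φ(u) du,

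evaluated by 61-point Gauss-Hermite quadrature. It was maximised over b at imposed values of the SD σ.

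**Layout 1: one row per fistula, scans as columns.**

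| SD | Intercept / w2 / w4 | Change in log-likelihood | AUC | Rank correlation with SD 0 | Largest change in population-averaged risk | Median P(patent) at effect 0 |
|---|---|---|---|---|---|---|
| 0 | 1.78 / 0.75 / 0.70 | 0 | 0.7866 | 1 | 0 | 0.844 |
| 1 | 2.08 / 0.88 / 0.81 | −0.034 | 0.7871 | 1.0000 | 0.011 | 0.877 |
| 2 | 2.76 / 1.16 / 1.05 | −0.097 | 0.7876 | 0.9999 | 0.023 | 0.931 |
| 4 | 4.52 / 1.90 / 1.70 | −0.135 | 0.7876 | 0.9999 | 0.028 | 0.986 |
| 8 | 8.39 / 3.63 / 3.15 | −0.165 | 0.7881 | 0.9996 | 0.026 | 1.000 |

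A 95% profile-likelihood interval excludes a value only when the log-likelihood falls by 1.96² / 2 = 1.92. The largest fall here is 0.165, so every SD tried is compatible with the data. The coefficients grow by 8.39/1.78 = 4.7, 3.63/0.75 = 4.8 and 3.15/0.70 = 4.5. These factors are nearly equal, so the change is mostly a rescaling. That is why ranking and AUC stay put while the risk at random effect = 0 does not.

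This set leans slightly towards SD 0. A second simulated set (156 fistulas, 82% patent) leaned the other way. Its log-likelihood went from −57.04 at SD 0 to −56.66 at SD 8, a rise of 0.38, and the week-2 coefficient went from 1.00 to 4.85. Chance can therefore send the estimate either way.

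**Layout 2: one row per scan, the single outcome copied.**

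| SD | Slope | Change in log-likelihood |
|---|---|---|
| 0 | 1.18 | 0 |
| 2 | 1.66 | +31.00 |
| 8 | 3.62 | +53.64 |
| 16 | 6.85 | +57.19 |
| 32 | 9.24 | +58.41 |

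The copies always agree, so the likelihood favours an ever larger SD. No interior maximum appears in the range tried. In the second simulated set the z-statistic of the scan measurement fell from 6.0 to 2.3 as the SD rose. Three further sets showed a fall from about 6 to 3. Significance is the criterion for choosing between the second and third scan, so in this layout that choice would lean on wherever the fitting stops.

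**The case against.** **A per-scan outcome may be meant.** The sentence "Patency will be assessed using the results from each US scan up to week 10" could be read as making patency at each scan the outcome. A participant effect would then be estimable. This stands as an ambiguity, but the article does not define the modelled outcome that way: "Mixed multivariable logistic regression will be used to model primary fistula patency by 10 weeks". It would also be a different model. Flow and vein diameter are among the scan measurements, and they also define patency, so same-scan values would predict a status that they themselves determine.

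**An analysis plan may specify the model differently.** It may, but the article states both the component and its reason, and the reason is wrong as written.

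**The practical harm is limited.** This largely stands. The article uses the score through an ROC cut-off and a PPV, which depend on ranking. In five further simulated sets covering both layouts (SD 0 to 8, measurement-only score), AUC moved by at most about 0.005. PPV in the 39 worst-ranked fistulas moved by at most one fistula (1/39 = 0.026). Rank correlation with the SD = 0 score was at least 0.996 with one row per fistula and 0.970 with one row per scan. A fit that returns zero variance is simply ordinary logistic regression.

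**Stronger readings.** A reader might infer three things that the documents do not support:
- That the phase II score would be arbitrary. Only coefficient scale and risk at random effect = 0 drift; ranking does not.
- That the apparent PPV would go to 100%. This needs fitted participant effects in the score. The article never says so, and it aims for a score built from as few measurements as possible.
- That the model could not serve as a calculator. New patients can be scored from the fixed part or by averaging over the random effect.

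**Conclusion.** The participant random effect is a stated model component with a rationale that does not fit the stated outcome. With one row per fistula its variance is practically not estimable: the log-likelihood moves by 0.17 while the coefficients grow about 4.5 to 4.8 fold. The coefficient scale and the absolute risk at random effect = 0 would then depend on chance and software. Ranking, AUC and PPV at an ROC-chosen cut-off hardly change. With the outcome copied to each scan row there is no usable finite variance estimate in the range tried, and the significance tests behind the scan choice are distorted.

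The primary patency rate, its exact interval and the figures 78, 312 and 347 are untouched. This is a should-fix.

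The sizes come from illustrative simulations with assumed effects and imposed SDs. No fit with the variance estimated was run, so failure to converge has not been shown. The conclusion also assumes one fistula per participant within a model; the article nowhere says otherwise.

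**What to change.** Delete the participant random effect. Fit ordinary logistic regression with one row per fistula, separately for wrist and elbow, and enter the week-2 measurements and the week-4 or week-6 measurements as separate covariates.

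If a per-scan patency outcome is really intended, define it. State which scan's measurements predict which scan's status, and state that phase II scores are population-averaged predictions that use no fitted participant effects.

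Penalisation and a centre effect are optional and do not bear on this point. The cost is one or two sentences in the protocol or analysis plan before model fitting, with no extra data or patients.

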### Definitions used within study

#### Primary patency

The interval between access creation to thrombosis event or first surgical/radiological intervention.

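### The risk model, its cut-off and its PPV have no at-risk set, so fistulas that have already failed can count as predicted failures

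*Protocol article*

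**What the plan says.** All references are to the protocol article.

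- **Population.** The Analysis plan section states "All analyses will be performed according to intention to treat" and defines the population as all enrolled, "including those whose fistula failed within the first 2 weeks postsurgery and those enrolled in error".
- **Failure.** The Definitions section gives primary patency as "The interval between access creation to thrombosis event or first surgical/radiological intervention". A thrombosed fistula has therefore already reached its outcome.
- **Scans after thrombosis.** If a trial scan shows thrombosis, the Blinding section says: "In such cases, no further study scans would be required". Clinical outcome data are still collected at week 10.
- **Predictors.** Under Analysis of primary and secondary outcomes, the model starts from the week 2 scan, and "further parameters from either the second scan or the third scan will then be considered". A ROC analysis then guides the cut-off, and the PPV is calculated there.
- **Missing scans.** The same section gives one reason for them: "It is anticipated that some participants will not attend all scans, and therefore, some scan data will be missing". Missing model parameters are to be "imputed using multiple imputation if the level of missing data is greater than 10" per cent. The level of missing data at each time point is also weighed when choosing which scans to use.
- **Early failures.** That section repeats the patency rate without fistulas that failed early. It gives no such restriction for the model, the cut-off or the PPV.

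**The concern.** A prediction made at a scan has meaning only for fistulas whose outcome is still open at that scan. The stated population has no such limit. A fistula that thrombosed before week 4 or week 6 has no flow or diameter to measure there, and its scan is absent because of the outcome, not because of non-attendance. If it is kept and its values are imputed, it enters the PPV as a failure that no one needed to predict.

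This matters because the risk score and cut-off carry over to phase II, which goes ahead only if ultrasound can identify at-risk fistulas (Study design). Phase II would act on fistulas that can still be salvaged, so the PPV it needs is the one among those. Whether failed fistulas are imputed into the model or left out also turns on a missing-data percentage that has nothing to do with which fistulas the PPV should describe.

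**Working it through.** **1. The plan's own figures (Sample size section).**
- Flagged fistulas needed: 1.96² × 0.72 × 0.28 / 0.10² = 77.4, rounded up to 78.
- Fistulas needed: 78 / 0.25 = 312. With 10% dropout: 312 / 0.90 = 346.7, rounded up to 347.
- Per site, an exact interval for 72% of 39 is 55.3% to 85.2%.

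All agree with the text.

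**2. The implied table.** Failures: 0.20 × 312 = 62.4. True positives: 0.72 × 78 = 56.16. False positives: 78 − 56.16 = 21.84. Implied sensitivity: 56.16 / 62.4 = 90%.

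**3. Direction.** At a fixed cut-off, a fistula that has already failed can be a true positive or a false negative, but never a false positive. If j such fistulas are flagged, they add j to both the numerator and the denominator of the PPV. The PPV therefore rises, or stays the same if j = 0.

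**4. Size.** Let k be the number already failed at the scan used. The documents do not give k, so the range is an assumption.

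- (A) All k are flagged: at-risk PPV = (56.16 − k) / (78 − k).
- (B) The k are flagged at the implied 90% sensitivity: at-risk PPV = 0.9(62.4 − k) / [0.9(62.4 − k) + 21.84].

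| k | Share of 312 | PPV, A | PPV, B | Flagged left, A | 95% half-width at PPV 72% |
|---|---|---|---|---|---|
| 5 | 1.6% | 51.16/73 = 70.1% | 51.66/73.5 = 70.3% | 73 | ±10.3 points |
| 16 | 5.1% | 40.16/62 = 64.8% | 41.76/63.6 = 65.7% | 62 | ±11.2 points |
| 31 | 9.9% | 25.16/47 = 53.5% | 28.26/50.1 = 56.4% | 47 | ±12.8 points |

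The half-width is 1.96 × √(0.72 × 0.28 / n flagged), against ±10 planned.

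**5. The 10% threshold.** 10% of 312 is 31.2 fistulas, which is 31.2 / 62.4 = 50% of the failures expected at a 20% failure rate. Scans missed for other reasons count towards the same threshold, so imputation may start with far fewer failed fistulas. The rule cannot tell the two kinds of absence apart.

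**6. Check of direction when the model is refitted.** An illustrative simulation used 312 fistulas, 20% failure, two scans and the top 25% flagged, with about 5% or 10% of the cohort already failed.
- Outcome included in the imputation: PPV 64% and 66%, against 52% and 39% in a model fitted to at-risk fistulas only.
- Outcome left out of the imputation: 56% and 45%, against 53% and 39%.

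The direction held in every scenario with failures before the scan. The levels should not be carried over to this study, partly because flagging a fixed 25% lowers the at-risk PPV as failures are removed.

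**The case against.** The strongest reply is that the article does not commit to the harmful steps and that an analysis plan would settle them. Much of this stands, and it rules out several stronger readings.

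- **Complete cases at or below 10%.** A reader might infer that failed fistulas are then dropped and that up to half the failures are wrongly lost. The article names no fallback. Leaving out fistulas that failed before the scan is also close to what a prediction model should do, provided it is done on purpose. The half depends on the 20% failure rate: at the 50% non-maturation the Introduction gives as an upper figure, 31.2 / 156 = 20%. Nearly full attendance would also be needed to stay under the threshold.
- **Thrombosis as a predictor.** The proforma records "presence of a flow limiting stenosis and fistula thrombosis", but the modelling text names no candidate parameters. That thrombosis would be one is an inference.
- **All fistulas that thrombose lack scans.** The scan that reveals thrombosis exists and is recorded. Only later scans are absent, and a scan that is not required need not be counted as missing.
- **The 72% is itself inflated.** It is a planning value, and the article does not say that it includes thrombosed fistulas.
- **The 10% trigger must go.** For fistulas still working, that is largely preference.

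What the reply does not remove is the text that is fixed: one population for all analyses, fistulas that failed before the first scan expressly included, and an imputation rule without an exception. The article separates early failures for the patency rate but not for the PPV. An analysis plan that followed these statements would inherit the problem.

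**Conclusion.** The point holds as a defect in the stated analysis population. Read literally, the model, cut-off and PPV include fistulas whose outcome is already settled. At a fixed cut-off that can only raise the PPV, or leave it unchanged, relative to fistulas still at risk.

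The direction follows from the definitions; the size does not. With about 5 failed fistulas the shift is roughly 2 points, small beside the planned ±10. With 16 it is about 7 points. With 31 it is about 18 points and takes the PPV below the planned lower limit of 62%. These figures assume that the reported PPV is 72% on 78 flagged and that all failed fistulas are flagged; at 90% flagged the shifts are about 2, 6 and 16 points. The documents do not show which case applies, nor that either side of the 10% threshold is bound to give an invalid model. The patency rate itself is not affected.

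**What to change.** Before the models are fitted, state the following:

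1. Each model, its ROC cut-off and its PPV are based on fistulas not yet thrombosed, abandoned or intervened on at the latest scan that the model uses.
2. Fistulas that failed earlier are counted and reported separately, by scan time and by wrist or elbow.
3. Scan values are not imputed after failure. Only scans missed by at-risk fistulas count towards the 10% threshold and are open to imputation.
4. If thrombosis was to be a candidate predictor, it is left out.
5. The expected precision is restated on the at-risk set, for example about ±11 points with about 62 flagged, instead of ±10.

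The population of all enrolled can stay for the patency rate.

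This needs analysis wording and no new data. The price is fewer failures per model: with a 50:50 split, (62.4 − 16) / 2 = 23.2 instead of 31.2 at k = 16, and (62.4 − 31) / 2 = 15.7 at k = 31. The interval will be wider and the reported PPV probably lower.
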